## Abstract

**Background:**

Self-stigma is highly prevalent in serious mental illness (SMI) and is associated with poorer clinical and functional outcomes. Narrative enhancement and cognitive therapy (NECT) is a group-based intervention combining psychoeducation, cognitive restructuring and story-telling exercises to reduce self-stigma and its impact on recovery-related outcomes. Despite evidence of its effectiveness on self-stigma in schizophrenia-related disorders, it is unclear whether NECT can impact social functioning.

**Methods:**

This is a 12-centre stepped-wedge cluster randomized controlled trial of NECT effectiveness on social functioning in SMI, compared to treatment as usual. One hundred and twenty participants diagnosed with schizophrenia, bipolar disorder or borderline personality disorder will be recruited across the 12 sites. The 12 centres participating to the study will be randomized into two groups: one group (group 1) receiving the intervention at the beginning of the study (T0) and one group (group 2) being a control group for the first 6 months and receiving the intervention after (T1). Outcomes will be compared in both groups at T0 and T1, and 6-month and 12-month outcomes for groups 1 and 2 will be measured without a control group at T2 (to evaluate the stability of the effects over time). Evaluations will be conducted by assessors blind to treatment allocation. The primary outcome is personal and social performance compared across randomization groups. Secondary outcomes include self-stigma, self-esteem, wellbeing, quality of life, illness severity, depressive symptoms and personal recovery.

**Discussion:**

NECT is a promising intervention for reducing self-stigma and improving recovery-related outcomes in SMI. If shown to be effective in this trial, it is likely that NECT will be implemented in psychiatric rehabilitation services with subsequent implications for routine clinical practice.

**Trial registration:**

ClinicalTrials.gov NCT03972735. Trial registration date 31 May 2019.

## Introduction

Mental illness stigma refers to the negative beliefs, emotional reactions and attitudes towards people with serious mental illness (SMI) endorsed by the general population (also referred to as public stigma [1]). People with SMI are generally acutely aware of public stigma and expect to be rejected by others (69.4% of the 1229 participants with schizophrenia (SZ) and 71.6% of the 1182 participants with mood disorders in the GAMIAN-Europe study had high perceived stigma [2, 3]). Self-stigma occurs when someone moves beyond awareness of stigma to accepting the negative stereotypes about SMI as true to describe him/herself [1]. Self-stigma refers to the process whereby a person’s previously held social identity (defined by social roles such as son, brother, sister, friend, employee or potential partner) is progressively replaced by a devalued and stigmatized view of oneself. Self-stigma is highly frequent in Europe (41.7% in SZ and 21.7% in mood disorders [2, 3]) and the USA (36.1% out of 144 people with SMI [4]). The ‘illness identity model’ [5] proposed that self-stigma can have pervasive effects on outcomes related to recovery from SMI, including self-esteem, hopefulness, social interaction, employment and symptom severity. The evidence consistently supports many of the model’s predictions, including that self-stigma is negatively associated with self-esteem, motivation to achieve personal life goals, shared-decision making, adherence into treatment, well-being, quality of life, personal recovery and social function [6–14]. People with elevated self-stigma report more dysfunctional attitudes, social withdrawal, depressive symptoms and increased suicidal ideation [5, 15–21]. High insight into illness directly predicts and compounds the effects of self-stigma on depression [15, 17, 22–24]. Impairments in cognitive functioning, metacognition and social cognition predict increased self-stigma [12, 24–29].

Several psychosocial interventions have been designed to reduce self-stigma and its impact on patient’s outcomes, with preliminary results on self-stigma, insight and self-efficacy [30]. Narrative enhancement and cognitive therapy (NECT) is a structured, 20 session group-based approach which combines psychoeducation to counteract SMI stereotypes, cognitive restructuring to challenge dysfunctional attitudes about the self and story-telling exercises to enhance meaning-making and the person’s ability to move beyond their illness-identity to a more integrated sense of self [31]. NECT is manualized and can be implemented with fidelity in routine treatment settings [31]. Four controlled studies, including three randomized controlled trials (RCT) in three different countries (USA, Israel, Sweden) have been published to date in psychotic-related disorders. NECT was effective in improving self-stigma, hope and self-esteem [32–34] with persisting effects after 6 months’ follow-up [33, 34]. The results on subjective quality of life were mixed, one study found improvements [32] but another found no effectiveness [33]. NECT was effective in reducing social withdrawal and avoidant coping strategies in participants with schizophrenia (SZ) in comparison with an active control condition [34]. However, NECT was not effective on social functioning, measured with the Quality of Life Scale [35], a global measure of psychosocial function [34]. In almost all studies of NECT, the samples were mixed, with some participants showing low levels of self-stigma (Internalized Stigma of Mental Illness (ISMI) total score < 2.5) and others moderate to high self-stigma (ISMI > 2.5). Changes in coping strategies were higher in participants from centres providing the intervention within the context of psychiatric rehabilitation [34].

In summary, NECT has demonstrated effectiveness on self-stigma and subjective aspects of recovery (hope, self-esteem and quality of life) in participants with psychotic-related disorders and SZ. Its effectiveness on social function and in other stigmatized SMI conditions (bipolar disorder (BD), borderline personality disorder (BPD)) are, however, still unclear. Similarly, NECT’s effectiveness in improving depression, treatment adherence, wellbeing and personal recovery is still unknown.

The objectives of the present study are to investigate (i) NECT effectiveness on social functioning in SMI participants, (ii) NECT effectiveness on self-stigma, psychiatric symptoms, depression, well-being, subjective quality of life and personal recovery, (iii) whether insight into illness and cognitive functioning at baseline predict improvements at follow-up and (iv) whether the effects on primary and secondary outcomes persist after 6 and 12 months’ follow-up.

The primary hypothesis to be tested is whether NECT significantly improves social functioning in comparison with the control group. The secondary hypotheses are to determine if, when compared to the control condition, NECT results in significant improvements in self-stigma, psychiatric symptoms, depression, wellbeing, self-esteem, subjective quality of life and personal recovery.

## Methods and design

### Design

This stepped wedge cluster randomized controlled study is multi-centric, prospective, interventional and exploratory. For ethical purposes, we have chosen a stepped wedge cluster randomized trial design, with a waiting list type control condition. Previous research from the French national REHABase network showed that (i) most patients were dissatisfied with their interpersonal relationships at the time of admission and asked for interventions improving social function [36] and (ii) elevated self-stigma was frequent (31.2% of the 738 participants [37]) and was negatively associated with recovery-related outcomes. Self-stigma has been negatively associated with patient’s longitudinal outcomes and to lower benefits from psychiatric rehabilitation [38]. Providing NECT to all participants aims at not excluding participants from interventions improving social function (e.g. social skills training or social-cognitive remediation) during the follow-up period without proposing them a credible therapeutic alternative (i.e. self-stigma reduction). This also aims at reducing potential deception bias and dropouts in participants allocated to the control group. Each centre will represent a cluster. In stepped-wedge RCTs, all clusters are evaluated before and after providing the intervention and each cluster switches from control to become exposed, but not at the same point in time [39, 40]. The 12 centres participating to the study will be randomized into two groups: one group (group 1) receiving the intervention at the beginning of the study (T0) and one group (group 2) being a control group for the first 6 months and receiving the intervention after (T1). The stepped-wedge design of this 2-group trial can be seen on Fig. 1.

**Fig. 1 Fig1:**
[figure not shown]
Diagram of the stepped-wedge trial design

The total duration of the study will be 18 months to allow for recruitment of the target number of participants, delivery of the intervention, follow-up assessments and data analysis using intention-to-treat methods. A schematic overview of the study design is presented in Fig. 2.

**Fig. 2 Fig2:**
[figure not shown]
Schematic overview of the study protocol

### Participants

#### Inclusion and exclusion criteria

Eligible participants will be adults (age > 18) diagnosed with schizophrenia, schizoaffective disorder, schizotypal disorder, schizophreniform disorder, bipolar I or II disorder or borderline personality disorder (DSM-5 criteria [41]). For the purpose of the study only stabilized outpatients will be recruited (defined as 3 months of clinical stability and no changes in pharmacological treatment in the past 3 months). Participants unable to give informed consent or with a comorbid intellectual disability will be excluded. Participation in other programs having an impact on social function or self-stigma (social cognitive remediation, social skills training) will be prohibited during the follow-up period.

#### Recruitment and randomization

Patients diagnosed with schizophrenia, bipolar disorder or borderline personality disorder (DSM-5 criteria [41]) will be recruited through six Rehabase psychiatric rehabilitation network centres [36], three FondaMental Academic Centres of Expertise (FACE) for SZ or BD [42, 43], one unit specialized in mood disorders at the Geneva university hospital, one psychiatric day-care clinic specialized in mood and personality disorders in Grenoble and one psychiatric rehabilitation centre located in the psychiatric hospital in Caen. The selected sites are already actively involved in treating patients with SZ, BD or BPD and have previous research experience in the field of psychiatric rehabilitation. Regular group meetings will be organized to monitor quality control and ensure good inter-rater reliability. A list of eligible participants will be generated under the supervision of the coordinating centre clinical research officer. Each eligible patient will be approached by a trained member of the research team and invited to participate in the study, thereby eliminating selection biases. Eligible patients will be given a leaflet describing the program and the research. Informed consent will be taken during a medical interview with one of the investigators. The clinical research officer of the coordinating centre (Grenoble) will be in charge of the randomization process for participants from all centres. Clusters will be randomized to receive the intervention at either T0 or T1. Stratified randomization will be used to ensure that cluster types are well balanced across groups. Outcomes will be compared in all groups at T0 and T1 (duration of intervention= 6 months). Six-month and 12-month outcomes for groups 1 and 2 will be measured at T2 (18 months after T0) to evaluate the stability of the effects over time. A 7-point improvement in social functioning measured using Personal and Social Performance Scale [44] (PSP) is generally considered as clinically significant. We plan to include 5 patients per centre and per group, meaning that there will be 10 participants included per centre for a total of 120 patients included (60 in group 1, 60 in group 2). This sample size was calculated using R package ‘pwr’ [45] based on Cohen [46] (*d* = 0.50, alpha level of 0.05) without allowing for intra-cluster correlations and the cluster and time effects found in stepped-wedge designs [47, 48]. This could be a considerable limitation, as it might have underpowered the trial [47]. Most of the outcome measures are self-rated questionnaires; the other evaluations will be conducted by an evaluator who has not taken part in the intervention. The schedule of enrolment, interventions and assessments is shown in Fig. 3 (SPIRIT diagram).

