#### Primary outcome

Social function will be assessed with the Personal and Social Performance Scale [44] (PSP), a clinician-reported measure of social dysfunction using six-point severity scale in four life domains (socially useful activities, personal and social relationships, self-care and disturbing or aggressive behaviours). PSP provides an overall rating score ranging from 1 to 100, higher scores representing better personal and social functioning. PSP showed acceptable internal consistency [52], excellent inter-rater reliability [53] and a satisfactory ability to detect changes [44]. A seven-point improvement during clinical trials is considered to be clinically significant [44].

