### Statistical analysis

Intention-to-treat analyses will be conducted in the first instance. The analyses will be conducted using parametric tests for normal distributed data (Student’s *t* and covariance analysis with repeat measures ANCOVA) and with non-parametric tests (Mann-Whitney *U* and Kruskal-Wallis test) in case of significant deviations from the normal distribution. The primary analysis was done by intention to treat.

We will analyse all outcomes using multilevel regression models with time point and intervention status as fixed effects and clusters as a random effect. Timepoint will be included as a categorical variable [39]. The statistical analysis will be done using the R software, version 3.2.3 [70]. The psych package version 1.5.8 will be used [71]. Effect size (Cohen’s *d*) will be calculated using the effsize package [71]. Size effects inferior to 0.20 will be considered as negligible, from 0.20 to 0.40 as small, from 0.40 to 0.60 as moderate and superior to 0.60 as strong [71]. The leaps package version 2.9 will be used for variable selection [72]. The level of confidence intervals will be set at 0.95 and the significance level of tests at 0.05.

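### The 120-patient size was computed as if patients were randomised individually and with no stated power; the 12-centre trial is not shown to have 80% power for d = 0.50

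*Protocol article*

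**What the plan says.** The sample size paragraph is in the protocol article under Recruitment and randomization. It reads "This sample size was calculated using R package ‘pwr’ [45] based on Cohen [46] (*d* = 0.50, alpha level of 0.05", and the result is "for a total of 120 patients included (60 in group 1, 60 in group 2", at 10 participants per centre. It gives no target power and does not say whether the test is one- or two-sided. The same paragraph concedes that centre and time effects were left out, with an "alpha level of 0.05) without allowing for intra-cluster correlations and the cluster and time effects found in stepped-wedge designs", and adds: "This could be a considerable limitation, as it might have underpowered the trial". It does not say how large the loss might be.

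Under Design, each centre is a cluster and the 12 centres are randomised into two groups. The abstract makes T0 and T1 the controlled comparison; T2 has no control group.

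Under Statistical analysis, all outcomes go into multilevel regression with time point and intervention status as fixed effects and cluster as the random effect. Repeated-measures ANCOVA is named as well. "The level of confidence intervals will be set at 0.95", with the "significance level of tests at 0.05".

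**The concern.** The calculation answers a question about 120 independently randomised patients. The trial compares six centres with six. Patients in one centre tend to resemble each other, and the treatment contrast is judged against variation between 12 centres, so 120 patients carry less information than the calculation assumes.

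The article keeps d = 0.50 as the planning effect. A reader facing a null primary result could take it as evidence against an effect of that size, although nothing in the article shows that the trial was likely to detect one. The analysis decides how much of the lost precision comes back, through the T0 PSP score. So the sample size statement and the primary model need to be settled together.

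**Working it through.** **Inputs from the article.** d = 0.50; alpha 0.05; 60 + 60 patients; 12 centres; 10 per centre; controlled comparison at T0 and T1; cluster as the random effect.

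**Assumptions (not in the article).** Two-sided testing, the natural reading beside 0.95 confidence intervals; six centres per group, inferred from 60/60 at 10 per centre; ICC 0.01 to 0.10; T0–T1 correlation 0.5 to 0.7.

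**1. The plan's own figure.** For a two-sample t-test, the noncentrality is d × √(n/2) = 0.50 × √30 = 2.739 on 118 df (critical value 1.980). Power is 77.5%, and the d detectable at 80% is 0.516. For 80% power, n = 63.77, so 64 per group (128). For 90%, n = 85.03, so 86 per group (172). A figure at or near 120 also arises from one-sided 85% power (118), or from one-sided 80% (102) inflated for 15% dropout (102/0.85 = 120). The intended target cannot be recovered from the text.

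**2. Centres as clusters, T1 scores only.** Design effect = 1 + (10 − 1) × ICC. Noncentrality = 0.50 × √(60/(2 × design effect)), on 12 − 2 = 10 df (critical value 2.228).

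| Assumed ICC | Design effect | Effective n per group | Power for d = 0.50 | Detectable d at 80% |
|---|---|---|---|---|
| 0 | 1.00 | 60.0 | 69.5% | 0.57 |
| 0.01 | 1.09 | 55.0 | 66% | 0.59 |
| 0.02 | 1.18 | 50.8 | 62% | 0.62 |
| 0.05 | 1.45 | 41.4 | 54% | 0.68 |
| 0.10 | 1.90 | 31.6 | 44% | 0.78 |

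The result does not hinge on the 10 df: with 118 df, power is 73.9%, 61.6% and 50.4% at ICC 0.01, 0.05 and 0.10.

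**3. The multilevel model on T0 and T1 with a centre effect only.** Centre means at each time have variance ICC + (1 − ICC)/10. If the centre effect is stable, their covariance is ICC. Generalised least squares with time and intervention fixed, on 10 df, gives:

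| Assumed ICC | No within-person correlation | Within-person 0.5, stable centre effect | Within-person 0.5, centre autocorrelation 0.8 |
|---|---|---|---|
| 0.01 | 66% | 81% | 79% |
| 0.05 | 59% | 79% | 73% |
| 0.10 | 56% | 79% | 66% |

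The first column is the model as written, treating a participant's two scores as independent given the centre. The other two show what using the within-person correlation adds.

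**4. T1 comparison adjusted for T0 PSP.** The variance in step 2 is multiplied by 1 − r², with the same r applied between and within centres. Example: ICC 0.05 and r = 0.6 give 1.45 × 0.64 = 0.928; noncentrality 0.50 × √(30/0.928) = 2.843; power 73%.

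| Assumed ICC | r = 0.5 | r = 0.6 | r = 0.7 | Detectable d at r = 0.6 |
|---|---|---|---|---|
| 0.02 | 75% | 81% | 89% | 0.49 |
| 0.05 | 66% | 73% | 82% | 0.55 |
| 0.10 | 54% | 61% | 71% | 0.63 |

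**The case against.** **120 is simply miscalculated.** A reader might infer this from 128 against 120. The documents do not support it: 80% power and two-sided testing are conventions that the article never states, and step 1 shows other unstated inputs that lead to 120 or close to it. Even on the conventional reading the gap is 8 patients, or 2.5 points of power. What stands is that the target is unstated.

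**The trial cannot detect d = 0.50 with usual power.** This too might be inferred, and it goes too far. The article gives no ICC and no T0–T1 correlation. Step 4 reaches 81% at ICC 0.02 with r = 0.6, and 89% with r = 0.7; step 3 reaches about 80% at within-person correlation 0.5 when centre effects are stable.

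**The weakness is already disclosed.** True, and it weighs in the sponsor's favour: readers are warned. But the warning covers only clustering and time effects and gives no size. It does not supply the missing power target.

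**The T1-only figures describe an analysis that is not planned.** Fair. Outcomes are compared at T0 and T1, and repeated-measures ANCOVA is named, so the low end of step 2 should not be read as the trial's power. However, the multilevel model specified for all outcomes names only cluster as a random effect. That model also stays below 80% when it gains nothing from within-person correlation.

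**A journal article condenses.** Target power and sidedness may be in the full protocol. But this article chose to report the calculation, and the mismatch with the cluster design is in what it does state.

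**Conclusion.** The point holds in a limited form. The sample size rests on individual randomisation, a design this trial does not have, and without a stated power target it cannot be checked. On the usual two-sided reading it delivers 77.5% before clustering. With 12 centres of 10, power for d = 0.50 is about 44% to 66% at assumed ICC 0.01 to 0.10 when the analysis makes no use of within-person correlation. A baseline-adjusted analysis gives about 54% to 89% over ICC 0.02 to 0.10 and correlation 0.5 to 0.7.

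The trial is therefore not shown to have 80% power, which is different from being shown to lack it. Every clustered figure depends on an ICC, and the adjusted ones also on a correlation, that the documents do not give. The firm parts are the unstated target, the calculation that ignores the randomised unit, and an acknowledged loss left without a size.

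**What to change.** Keep 120 patients and make two changes.

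1. In Recruitment and randomization, state the target power and sidedness. Replace the pwr statement with power or detectable d for 6 versus 6 centres of 10, over a stated range of ICC and T0–T1 correlation, with both labelled as assumptions. For example: under independence and two-sided 0.05, 120 patients give 77.5% power for d = 0.50; with 12 centres of 10, assumed ICC 0.02 to 0.10 and T1 analysis adjusted for T0 PSP, power is about 54–75% at an assumed T0–T1 correlation of 0.5, 61–81% at 0.6 and 71–89% at 0.7; at 0.6 the effect detectable with 80% power is d of about 0.49 to 0.63.

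2. In Statistical analysis, make the primary PSP analysis a model of T1 scores with a centre random effect and adjustment for T0 PSP. Alternatively, use a T0–T1 model with a participant random effect as well as the centre effect.

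The cost is a less favourable stated figure and a few lines of text, with no extra patients. According to Trial status, recruitment had not begun, so both changes could be made before any data are seen.

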
**Fig. 3 Fig3:**
[figure not shown]
Schedule of enrolment, interventions and assessments (SPIRIT diagram). BIS, Birchwood Insight Scale; ISMI, Internalized Stigma of Mental Illness; MARS, Medication Adherence Rating Scale; NECT, narrative enhancement and cognitive therapy; PSP, Personal and Social Performance Scale; S-QoL, Subjective-Quality of Life; TAU, treatment as usual; TMT, Trail Making Test; V-SIR, Versailles-Situational Intention Reading; WAIS IV, Wechsler Adult Intelligence Scale-4th edition; WEWMBS, Warwick-Edinburgh Mental Wellbeing Scale; YMRS, Young Mania Rating Scale

### NECT

#### Translation procedure

A consistent translation and cross-cultural adaptation procedure was realized by two independent research teams ([name] in Grenoble; [name] in Geneva). All materials were translated from English into French, the first language of all translators. Each team reviewed the material translated by the other team so all translations were crosschecked. Regular group meetings between the two teams were conducted to discuss any problematic translations and resolve any disputed items, in line with established translation methods.

